## Abstract

**Background:**

The current research concept of mentalization is used in the study to clearly identify affective and cognitive abilities of the caregiver-child dyad with the aim of compensating deficits on both sides with psychological-psychotherapeutic strategies.

**Methods:**

The objective of this explorative, longitudinal intervention study is to provide an in-depth understanding of the psycho-social background of 30 children aged 6–12 years living in institutional or family-centered foster care. Data will be collected at three time points: before, after and 12 months after participating in the newly developed group intervention, which intends to address the particular needs of children of drug abusing parents living in foster care in the latency period. The study is conducted at the Faculty of Psychology of the University of Vienna in collaboration with the Association “Dialogue” (Verein Dialog). The treatment duration spans 5 months, during which two specifically trained psychotherapists conduct 10 group sessions for children and three group sessions for foster caregivers. All statistical analyses will consider the type of data available. Therefore, the primary outcome of the study will be assessed via the Friedman test due to the ordinal dependent variable as it is the non-parametric alternative to the one-way ANOVA for repeated measures. In addition, the Mann–Whitney U test is used to compare differences between two independent groups (children living in institutional foster care vs. family foster care). To assess potential correlations regarding the child and caregivers’ capacity to mentalize, Spearman correlations (ρ) are conducted. To examine the secondary outcome, apart from the methods previously outlined, we will also utilize qualitative thematic analysis.

**Discussion:**

The present study uses the current research concept of mentalization to identify affective and cognitive abilities of the caregiver-child dyad with the aim of compensating deficits on both sides with psychological-psychotherapeutic strategies. There are some limitations of the study to mention: the small sample size does not allow to generalize the results. Due to the lack of a comparison group, a randomized control study (RCT) was not conducted. The authors are aware of these limitations. However, the studies’ findings, will help to deduce research questions for further studies.

## Introduction

1

Foster care is government-subsidized and -regulated temporary care for children who have been removed from their families for reasons of abuse and neglect. Children can be placed either in family or residential care. While family foster care includes arrangements of children living with unrelated foster parents (nonrelative foster care), with relatives (kinship care), or with families who plan to adopt them (foster/adopt homes), residential programs encompass a type of living in out-of-home care placement in which specialized services for youth with emotional and behavioral problems or other special needs are provided in a highly structured environment. It was estimated that in 142 countries about 2.7 million children aged 0–17 could be living in institutionalized care worldwide (Petrowski et al., 2017).

In Austria, in 2021 a total of 12,871 minors were living in foster care (of which 31.5% only in Vienna): 61.3% of the children and adolescents were placed in institutional group care, while 38.7% were accommodated with foster families (Österreich, 2022). In terms of age, 44.3% of children in foster care, were between the ages of 6 and 14. Children placed into institutional care usually live together with 8–10 other children, cared for by a team of social pedagogues, each of them having one main contact person, called “caregiver.”

Although estimates vary widely, a detailed literature search suggests that parental substance use disorder plays a major role in the child welfare system (Seay, 2015).

Maltreatment, such as neglect, and placement into foster care are considered as traumatic affecting children’s immediate and future psychosocial development and mental health (Cicchetti and Toth, 1995; Bowlby, 1998; Cicchetti et al., 2006). Children placed in foster care might have experienced distressing feelings such as confusion, anxiety and sadness, due to the unfamiliar or previously experienced situation to which they are adapting as a result of their placement (Bruskas, 2008). High rates of internalizing problems (e.g., anxiety, depression), externalizing problems (e.g., aggression, impulsivity), poorer social skills, and lower adaptive functioning were also reported among foster children compared to children who did not experience replacement (Webb et al., 2010; Jones Harden et al., 2014).

Specifically, those children who experienced trauma frequently revealed underdeveloped mentalizing capacities (Ostler et al., 2010). Muller et al. (2012) specified that their ability to cope with physical, or emotional traumas highly correlated with the perceived quality of their current relationships, and that traumatic experiences had a major impact on attachment behaviors of out-of-home children toward their foster caregivers. As a result of the children’s adverse experiences with parental care, they may be inclined to avoid forming new and supportive relationships. This creates a complex situation for all individuals involved, including both the foster caregiver and the children. On the other side, foster parents and institutional caregivers know that foster care is mostly not permanent. This issue may interfere with attachment formation to the foster parents/caregivers (Åkerman et al., 2020).

The ability to mentalize plays a crucial role in individuals’ coping abilities with traumatic events (Pecora et al., 2005; Szilagyi et al., 2015). Mentalization can be understood as “the ability to understand the actions by both other people and oneself in terms of thoughts, feelings, wishes and desires” (Bateman and Fonagy, 2016, p. 3). By involving the internal regulation of emotions through thoughts, children as well as adults who are able to mentalize are more resilient and able to tolerate feelings of anger, fear, shame, and distress resulting from adversity and trauma (Allen et al., 2008; Brockmann and Kirsch, 2010; Ostler et al., 2010; Ensink et al., 2017; Giusti et al., 2021).

Research revealed a strong association between insecure attachment representations and struggles of drug addicted parents in responding to their children’s emotional cues (Grienenberger et al., 2005; Slade et al., 2005), which in turn interfere with the ability to form secure attachments and mentalizing skills in children (Madigan et al., 2007; Bammens et al., 2015). However, most studies have focused mainly on the characteristics of the child, neglecting the parents’ variables (Schmidt and Schimmelmann, 2015).

Pediatricians reported that children of drug-using families were often distressed by their parents’ substance use. They often had to take on parental roles, due to their parents’ incapacity. As they usually have blamed themselves for their parents’ behavior and felt responsible for their wellbeing (Smith and Wilson, 2016), they tended to keep the situation secret and not show their distress in public (Morrison et al., 1996; Hoffmann and Su, 1998). They also tended to self-stigmatize and live in fear of “failing” in the same way as their parents did (Matthews et al., 2017). Within addiction care, children of drug abusing parents are not always seen as individuals in need due to the fact, that the focus stays on the consuming adult. Nevertheless, detecting problems in children early as well as prompt implementation of prevention or treatment programs, would increase the likelihood of the child growing up safely (Van de Meer et al., 2019). Moreover, children of parents with Substance Use Disorder (SUD) experience a notably higher incidence of physical, emotional, and sexual abuse, as well as emotional or physical neglect (McGlade et al., 2009; Altshuler and Cleverly-Thomas, 2011). Therefore, foster care children of drug abusing families, place an additional strain on the healthcare system, thus more research identifying factors enabling children and adolescents to enhance their mental wellbeing and healthy development, as well as cost-effective treatment options, is needed.

Parental attitudes represent the primary social influence encountered by the child during their formative years (Zunich, 1966). As Farmakopoulou and Baltsioti (2024, p. 319–320) emphasize clearly: “Foster carers play a crucial role in this institution, and their experiences, perceptions, and relationships are vital for the wellbeing and development of the children under their care. Understanding foster carers’ views on factors that support or hinder successful fostering is essential for grasping the dynamics of foster care.”

Children’s ability to mentalize can be best observed during the latency period in child development. The latency period takes place between the age of 6 and 12 and is characterized by a number of new developmental challenges, such as finding a place in a peer group, realizing cognitive activities, and compliance to the rules of the family and the community. Individuals’ ability to cope with these challenges largely depends on the ego-function development, reflected, e.g., in emotional control, ability to deal with frustration and being able to reflect on the other’s perspective (Akhtar, 2009; Dejko et al., 2016).

Studies reported that a parent’s ability of reflective functioning (RF), as mentalization is operationalized, predicted children’s attachment security and mentalization ability (Grienenberger et al., 2005; Slade et al., 2005; Allen et al., 2008), and various aspects of a child’s short- and long-term development (Fonagy et al., 1991; Slade, 2002; Steele and Steele, 2008). Improvements in RF related to mothers with SUD were associated with improvements in caregiving quality (Åkerman et al., 2020). The studies mentioned above looked in samples of biological or foster parents. The majority of interventions that have been developed to support foster carers has been criticized for their lack of focus on improving the capacity of carers to respond to the child’s related needs while it is obvious that keeping the needs of a child in mind is the best support for every child’s development RF and social skills, such as reflexibility and social orientation, help every carer to understand behavior as a respond to emotional needs instead of just seeing “naughty” or “bad” behavior and the child itself feels understood and valued (Adkins et al., 2018; Midgley et al., 2019).

RF is defined as the ability to mentalize in the context of close, interpersonal relationships. With the words of Fonagy et al. (1998), RF helps us “to distinguish inner from outer reality, pretend from “real” modes of functioning as well as intra-personal mental and emotional processes from interpersonal communications” (Fonagy et al., 1998, p. 4). A recent study, showed that a group of brief psychoeducational parenting intervention increased RF in foster parents and improved parental sensitivity while decreasing children s’ internalizing behavior (Adkins et al., 2022).

Research on attachment and mentalization in substance-abusing families is emerging. While studies exist on mentalization in substance abusing mothers (e.g., Suchman et al., 2006; Pajulo et al., 2012; Suchman, 2016), research on mentalization or reflective functioning in children of substance-abusing parents is still lacking, and evidence suggest the specific need for interventions aimed to address experiences and feelings associated with foster care in children (Ostler et al., 2010).

Mentalization-based treatment (MBT) programs to increase ego-functions have been developed and implemented for multiple indications such as borderline personality disorders, drug addiction, and for children with parents suffering from mental health disorders (e.g., Bateman and Fonagy, 2008, Bruskas, 2008; Suchman et al., 2010). They aimed to understand and improve the individual’s ability to reflect upon their own and others’ feelings, thoughts, and desires. When applied to children and their caregivers, MBT focus on replacing destructive habitual ways of feeling and acting by improving mentalizing abilities, together with the individual’s emotional wellbeing, and interpersonal skills (Mayes, 2012).

A Narrative Systematic Review (Midgley et al., 2021) examined the range of mentalization-based interventions for children in middle childhood (6–12 years). According to this review, a relevant number of mentalization-based interventions have been conducted in the context of fostering and adoption, but the childrens’ mentalizing capacity was hardly ever assessed as an outcome and children from drug abusing families are still lacking as target group. This lack was already mentioned in previous publications (Jacobson et al., 2015; Midgley et al., 2017), but did not change so far.

## Methods/design

2

### Aims

2.1

The first aim of this study is to explore the development longitudinally of the children’s mentalization ability at three measure time points: before, after and 12 months after attending a newly developed group MBT-intervention. It is an adapted version of Midgley et al. (2017). Mentalization-Based Treatment for Children (MBT-C), which addresses the particular needs of children of substance using parents, who live in foster care during middle childhood, integrating the psycho-social background of children living in foster care. Second, we will explore the mentalization capacity of the caregivers, their attitudes on drugs and drug addiction, and their social skills (e.g., social orientation and reflexibility) with regard to the impact on the children’s mentalization at the beginning of the intervention to better understand whether it influence the development of mentalization over time.

### Participants

2.2

In the study 30 children living in foster care (institutional or foster home) and their actual main foster caregiver will be included (*N* = 60).

Children’s inclusion criteria for participation are: (1) age between 6 and 12 years, (2) stable mental health status (e.g., no psychotic state), (3) living in foster care for at least 6 months. A minimum of time in a stable and persistent placement needs to be considered to assure the children’s ability to reorganize their internal world and behavioral outcomes (Cassibba et al., 2023). Caregiver’s inclusion criteria are (1) child lives in the same household and (2) 18 years of age or older. Children are excluded from the study if presenting neurological, cognitive, and/or psychiatric problems, and/or difficulties reported by their caregiver.

Children in middle childhood, aged between 6 and 12, are very common as primary target of mentalization-based treatments. However, middle childhood has received only limited attention regarding the ability to mentalize (Midgley et al., 2021).

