### Measures

2.3

Relevant biographical data are collected at baseline within a clinical interview. They included the children’s age at the first out-of-home placement, substance use dependency syndrome of biological parents and the number of caregivers since out-of-home placement. Data Research Topic is conducted by specifically trained clinical psychologists and psychotherapists.

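### The 6-month entry rule counts total time in foster care, but its stated reason is time in a stable placement, so a recently moved child can enter and any settling-in cannot be told from programme change

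*Protocol article*

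**What the plan says.** The Participants section of the protocol article sets three entry criteria for children. The third is "3) living in foster care for at least 6 months". The sentence that follows gives the reason: "A minimum of time in a stable and persistent placement needs to be considered", so that the child has had time to reorganise inwardly and in behaviour.

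For caregivers the section asks that "child lives in the same household" and that the caregiver is an adult. The person enrolled is the current one ("their actual main foster caregiver will be included"), and no minimum time with the child is given.

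The Introduction recognises that "foster care is mostly not permanent". It describes children in care as distressed "due to the unfamiliar or previously experienced situation to which they are adapting as a result of their placement". The Measures section lists the biographical data taken at baseline: age at first out-of-home placement, substance dependence of the biological parents, and "the number of caregivers since out-of-home placement".

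The Procedure section puts T1 at baseline, T2 within one month after a 20-week programme and T3 at 12 months. The statistical plan compares RF across the three times with a Friedman test and uses equivalent quantitative methods for secondary outcomes. The Abstract states that there is no comparison group.

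**The concern.** The rule and its reason measure different things. The rule counts months since the child came into care. The reason is about months in one lasting placement. A child two years in care who changed family or residential unit three weeks before T1 satisfies the rule, yet is in the state the reason is meant to keep out.

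This matters because each child is compared only with itself over time. If some children are measured at T1 while adapting to a new home and at T2 once settled, the change adds to whatever the programme does. The Mentalization-based group intervention section expects symptoms to fall and RF to rise. A fall in symptoms is also what settling-in would be expected to produce.

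The CBCL is exposed in a second way. It is a caregiver report, so after a recent move the T1 form may come from someone who has known the child only briefly.

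**Working it through.** **1. Does the rule imply its reason?**

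- Let C be the time in foster care at T1 and P the time in the current placement at T1. Always P ≤ C, with equality only for a child who has never moved within care.
- The rule is C ≥ 6 months. The reason, applied to the placement the child is in at T1, needs P to be long enough.
- C ≥ 6 months does not imply P ≥ 6 months. In the example above C = 24 months and P is about 0.7 months.
- The word current is an interpretation; the article speaks of a stable and persistent placement. For a child who has just moved, however, the current placement cannot yet be called persistent.

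**2. Does anything else in the article close the gap?**

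| Element | Effect on a recently moved child |
|---|---|
| Caregiver criteria | Same household and adult age only; no minimum duration |
| Stable mental health criterion | Exemplified by absence of a psychotic state; says nothing on placement |
| Exclusion for psychiatric problems or caregiver-reported difficulties | May remove a child in marked distress after a move, but not every moved child |
| Listed baseline data | Age at first placement and number of caregivers do not give the time in the current placement |
| Friedman test | Time as within-subject factor, with family versus residential care named as between-subject factor; no term for placement time |
| Historical control data (Discussion) | Would help only if comparable on placement time, which is not described |

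Some of these protect in part. None makes the rule deliver its reason.

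**3. How long is the window from T1 to T2?**

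The programme lasts 20 weeks, and 20 / 4.35 = 4.6 months; the article also calls it 5 months. Adding up to 1 month for the T2 assessment gives roughly 5 to 6 months. That is close to the 6 months the protocol itself sets, so a child who moved just before T1 would pass through most of the settling period between T1 and T2.

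**4. How many children could be affected?**

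The article gives no move rate, so this step is illustrative. Assume an annual probability r of changing placement, constant over the year. The share who moved in the 6 months before T1 is 1 − (1 − r)^0.5. The sample is 30 children ("In the study 30 children living in foster care").

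- r = 20%: 1 − 0.8^0.5 = 0.106, and 0.106 × 30 = 3.2 children.
- r = 40%: 1 − 0.6^0.5 = 0.225, and 0.225 × 30 = 6.8 children.

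That is about 3 to 7 of 30. The true figure could lie outside this range. It would be lower if the health criteria screen out unsettled children.

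**5. Which outcomes?**

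- CBCL: a caregiver's report of emotional and behavioural problems. The Introduction links adaptation to placement with confusion, anxiety and sadness, so a settling-in effect is plausible.
- RF: coded from an interview about attachment experiences. The Primary outcome section reports stability in children as high over 3 months and adequate over 12. Nothing in the article shows RF rising after a move, so an effect is possible but inferred.

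**The case against.** The strongest reply is that the two sentences belong together. The second may explain how criterion (3) is applied, with the full protocol holding the operational definition. That may well be the intention. But the sentence sets no duration and is not worded as a criterion, so anyone screening from the text as it stands would admit the moved child. If a placement rule was meant, writing it down settles the matter.

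Several stronger readings are tempting, and the documents do not support them:

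- A reader might infer that newly moved children do enter and that their settling-in will be reported as programme effect. The article reports no such child and no move rate. It supports only that they can enter.
- A reader might take the 6-month rule as the only safeguard against natural recovery. It is the only criterion aimed at placement time, but the health criteria and the historical controls offer partial protection.
- A reader might take the recorded number of caregivers as proof of moves. In residential care a team looks after the child, so the count can rise through staff changes within one unit.
- A reader might conclude that placement dates are not collected. The list of biographical data need not be exhaustive, so this is not established.
- A reader might want 6 months with the same caregiver as well. The stated reason concerns placement. Such a rule could exclude children in a stable residential unit because a key worker changed, and so fall unevenly on one side of the family versus institutional comparison.

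It is also fair to say that the study is explorative, that the small sample and missing comparison group are declared limits, and that maturation remains under any entry rule. This limits what the correction can achieve. It does not justify an entry rule that misses its own stated purpose.

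**Conclusion.** The concern holds as a mismatch between an entry criterion and its stated reason, with a possible bias that the design cannot detect. That the rule can admit recently moved children follows from the text alone.

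The size of any bias is unknown. The count of 3 to 7 children rests wholly on the assumed move rates and says nothing about how far each child's score would shift. The expected direction, towards apparent benefit, is reasonable for the CBCL and speculative for RF, the primary outcome. The point is worth correcting because the correction is simple and the analysis has no other means of separating the two sources of change.

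**What to change.** 1. Reconcile the criterion with its reason: require at least 6 months in the current placement (family or residential unit) at T1. Do not add a minimum time with the same main caregiver.
2. Make sure the baseline form holds two dates: the start of the current placement and the start of the current main caregiver's role. Obtain them retrospectively for children already enrolled; the Discussion mentions initial findings, so the study is under way.
3. Repeat the RF and CBCL time comparisons without children who had under 6 months in their current placement at T1, and report how many were left out. Use the caregiver date descriptively, to show how well T1 informants knew the child.

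The cost is one amended criterion, two dates and one sensitivity analysis. A few recently moved children would have to wait or would not be enrolled. Under the assumed rates the sensitivity analysis would keep about 23 to 27 of 30 children (30 − 7 and 30 − 3), before any dropout. It would therefore be somewhat less precise and should be read alongside the full analysis, not in place of it.
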